## Methods/design

A pre-post intervention study design is used where HPV vaccination initiation and completion rates are measured before and after the intervention across the same clinics and enrolled participants (Fig. 1). HPV vaccination uptake 18 months before intervention will be queried from electronic medical records (EMR) and Georgia Registry of Immunization Transactions and Services (GRITS), which will serve as the historical control. GRITS is a population-based web application containing consolidated demographic and immunization history information. The use of a concurrent control is to reassess the background HPV uptake rate among PLWH during an adjacent time-period to post-intervention and similar population resources. The comparison of HPV vaccination rates pre- and post-intervention in the three selected representative HIV clinics in Georgia will be an exploratory goal of the trial due to the retrospective approach in the control phase and the prospective approach in the post intervention phase. A “within” analysis will be conducted to compare sites both pre- and post-intervention.

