### Patient-level intervention approach

Eligible and consenting participants (*n* = 365) will be part of the intervention group and will receive recommendation for the HPV vaccine from providers and clinic staff. Enrolled participants will also complete a self-administered questionnaire at enrollment on a HIPPA compliant online data management database on a tablet device. The survey questions will include sociodemographic characteristics, knowledge of and attitudes towards HPV, HPV vaccination, and anal cancer, and vaccine hesitancy. Participants will be requested to provide consent for their HPV vaccination history to be verified with electronic EMR and GRITS. Participants will then watch a short video on HPV and HPV vaccination that can be viewed on their phones (or the study’s tablet device) while waiting to be seen. Potential participants will be asked to follow the study’s private Facebook page which offers additional educational information tailored towards individuals with HIV on HPV-related disease and general health promotion, and risk reduction tips. The Facebook page will also utilize Facebook Messenger (commonly known as Messenger). The proposed study will utilize Messenger to send reminders for follow up appointments for the next shot in the series and motivational messaging to encourage and promote receipt of the HPV vaccine. Participants will be contacted to complete a post-evaluation survey administered via online, telephone, or a mailed paper copy at 6–9 months after baseline. Participants will receive $25 incentive for completion of baseline and follow up study activities.

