#### Data analyses of primary outcomes

For analysis of the primary (HPV vaccination initiation) and secondary endpoints (HPV vaccination completion), the uptake rate of HPV vaccination pre- and post-intervention will be estimated separately with a 95% exact confidence interval using all eligible cases from both phases. The one-sample binomial exact test will be used to test whether the rate after the intervention is higher than the baseline rate (P0 = 13.5%). We will also perform the Chi-square test to compare the rate change between control and interventional phases, which will be exploratory. Logistic regression will be used to further adjust background difference in study population in pre- and post- intervention phases. For the longitudinal data collected from the intervention phase, the data structure holds multi-level information from patients, providers, and clinic levels. The goal of the analyses is to identify the factors that might impact HPV uptake from each level of information, which might lead to the future improvement of implementation strategy. Data will be described using summary statistics (e.g., quartiles, median, mean, standard deviation) for continuous variables and marginal distribution (frequency and percentage) for categorical variables. The univariate association with the HPV vaccination (yes vs. no) will be tested in logistic regression for each variable separately. The change of survey response between baseline and a follow-up time point will be tested by paired tests (e.g., paired t-test, McNemar test). Along with data visualization, all above mentioned descriptive and univariate association analyses will be repeated within each of the three clinics. Data will be pooled to build the multilevel analysis models, we mainly consider using the mixed-effect model and/or Bayesian multilevel modeling, in which the random effect will be considered at provider and clinical levels. We will follow the key modeling considerations listed by J.J. Hox [29] to identify the significant mediators and moderators at different levels that impact the uptake of HPV vaccination.

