#### Statistical power

Based on our preliminary data, we found that HPV vaccination rate is around 13.5% (P0) in general, and another larger study in the literature found a very similar rate of 13.6% [10]. We powered the study to detect an uptake rate > 13.5% after the intervention. Thus, a sample size of 317 achieves 80% power to detect a superiority difference of 5% (PB-P0) using an exact one-sided test with a significance level (alpha) of 0.05. We anticipate a 5% superiority difference is reasonable to achieve with an uptake rate of 18.5% (PB) after the intervention. We will be able to reject the Null hypothesis and claim the uptake rate of > 13.5% after 54 patients have initiated the HPV test. After taking about 15% of the drop-off rate into account, we plan to include 365 participants among 3 clinics for the intervention phase. The calculation was by PASS 2020 for testing superiority of one proportion using the Exact test. The Null hypothesis is *P* < = 13.5% and the alternative hypothesis is *P* > 13.5%. For the control phase, we will query all eligible subjects from EMR database among the 3 clinics at 18 months pre-intervention, which could be approximately 2300 subjects [30]. Assuming we end up with the same number of subjects in both control (*N* = 317) and intervention phase (*N* = 317), we will have 81% statistical power to detect an HPV uptake rate difference of 9% (22.5% vs. 13.5%) by two-sided Fishers’ Exact Test and under significance level of 0.05. We anticipate such a difference would be feasible based on our best knowledge and the literature. Regarding the patient- level component of the intervention, all incoming eligible patients will be influenced, and hence 365 participants are the minimum number to capture the follow-up information, the actual number of sample size used for the calculation of HPV vaccination rate will be larger as the vaccination status will be captured automatically in EMR without a consent.

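### The plan does not fix whether consenting enrollees or all eligible EMR patients are tested against 13.5%; if enrollees are used, consent selection can pass for a programme effect

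*Protocol article*

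**What the plan says.** All places are in the protocol article.

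**Control phase.** Statistical power: "For the control phase, we will query all eligible subjects from EMR database among the 3 clinics at 18 months pre-intervention". The section puts their number at about 2300.

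**Post-intervention phase, pointing to enrollees.**
- Methods/design: rates are "measured before and after the intervention across the same clinics and enrolled participants".
- Patient-level intervention approach: "Eligible and consenting participants (*n* = 365) will be part of the intervention group". These people complete a survey, watch a video and are paid $25. The same section adds: "Participants will be requested to provide consent for their HPV vaccination history to be verified with electronic EMR and GRITS".
- Statistical power: the primary test needs 317 patients, raised to 365 participants for about 15% drop-off, and succeeds at 54 initiations.

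**Post-intervention phase, pointing to all eligible patients.**
- Data analyses of primary outcomes: both rates are estimated "using all eligible cases from both phases".
- Statistical power, last sentence: 365 is only a minimum for follow-up information, and "the actual number of sample size used for the calculation of HPV vaccination rate will be larger" because vaccination status can be read from the EMR with no consent.

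**Tests.** The confirmatory test is a one-sample exact binomial test against a fixed 13.5%. The chi-square comparison of the two phases is exploratory. Logistic regression is to adjust for population differences; Process evaluation names age, gender, race and insurance.

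**The concern.** The population, test, sample size and success count are all stated in the article, and they do not fit together. A count of 54 has meaning only for a group of about 317. A rate over all eligible EMR patients has a different denominator and needs a different threshold. As written, either group could be chosen, even after the results are known.

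The choice matters because the groups differ in a way tied to the outcome. Agreeing to join an HPV-vaccine study is plausibly related to being willing to have the vaccine. Enrollees could therefore show uptake above 13.5% even if the programme did nothing. A one-sample test has no comparison arm in which that selection would cancel. In the exploratory comparison, the same volunteers would be set against an EMR control not selected by consent. The named covariates do not measure willingness to be vaccinated. Aim 2 asks about uptake among people living with HIV, which a volunteer cohort alone does not answer.

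**Working it through.** **1. The plan's own figures** (P0 = 0.135, PB = 0.185, one-sided alpha 0.05, 80% power).
- Normal approximation: N = ((1.645·√(0.135·0.865) + 0.842·√(0.185·0.815)) / 0.05)² = 316.05, rounded up to 317. The stated N reproduces.
- Exact threshold at n = 317: P(X ≥ 53 | 0.135) = 0.0585 and P(X ≥ 54 | 0.135) = 0.0425. So 54 is the right count for 317, and the chance of success at a true rate of 13.5% is 4.2%. (Exact power at 18.5% is 77.0%; that is a separate matter.)
- 317 × 1.15 = 364.6, the planned 365. The rule therefore belongs to the enrolled cohort.

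**2. If enrollees are tested.** Assumptions: no programme effect; 13.5% of all eligible patients would be vaccinated anyway; 365 of 2300 consent (f = 0.1587); the eligible pool after the start is about the size of the control pool. Let a and b be the consent probabilities of those who would and would not be vaccinated. Solve
- a/(1−a) = OR · b/(1−b)
- 0.135·a + 0.865·b = f

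Enrolled uptake is then 0.135·a/f, and the chance of success is P(X ≥ 54 | n = 317, enrolled uptake).

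| Assumed consent OR | a | b | Enrolled uptake | Chance of success |
|---|---|---|---|---|
| 1 | 0.159 | 0.159 | 13.5% | 4.2% |
| 1.25 | 0.186 | 0.154 | 15.8% | 30% |
| 1.5 | 0.210 | 0.151 | 17.9% | 67% |
| 2 | 0.252 | 0.144 | 21.4% | 98% |

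An odds ratio of 1.5 alone brings uptake close to the planned 18.5%. Put as a ratio of uptake in enrollees to uptake overall, 1.1 gives 15.5% false success and 1.2 gives 36.6%.

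**3. If all eligible EMR patients are tested.** Consent selection drops out. At an assumed n of 2300, 54 initiations would be 54/2300 = 2.3%, far below 13.5%. The exact threshold is 339 (339/2300 = 14.7%; P(X ≥ 339 | 0.135) = 0.045), and power at 18.5% exceeds 99.9%.

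**4. Why the reference rate must follow the same rule.** Suppose 13.5% had been computed over attenders and non-attenders, only attenders are vaccinated, and the post-intervention analysis counts attenders only. With no programme effect:
- 90% attend: n = 0.9 × 2300 = 2070; rate 0.135/0.9 = 15.0%; exact threshold 306; false success 62%.
- 80% attend: n = 1840; rate 0.135/0.8 = 16.9%; exact threshold 274; false success 99%.

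The documents do not give the denominator of the 13.5%. These two lines show only what a mismatch would do in a large sample.

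**The case against.** The tempting stronger reading is that the intervention rate does come from consenting patients, and that the success rule sets them against the 2300 EMR controls. The documents do not support either half.
- The primary-analysis section and the last sentence of the power section both point to all eligible patients without consent. On that reading there is no consent selection.
- The 54-of-317 rule tests a fixed 13.5%. The comparison with the EMR control phase is labelled exploratory, and Methods/design gives the reason: one phase is retrospective and the other prospective.

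A reader might also infer that the control includes patients who made no visit, so that counting attenders inflates the rate. The article does not say so. The power section says only that all eligible subjects are queried, and it attributes 13.5% to preliminary data without a denominator.

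Finally, the consent odds ratios are not in the documents.

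All of this stands and sets the limits of the point. It does not remove it. The enrollee reading is supported by the design statement, by the definition of the intervention group and by the only sample size and success count given. The scenarios are assumptions shown as a range, but a modest departure from 1 already moves the error rate well above its nominal level. Calling the pre/post comparison exploratory does not protect the binomial test.

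**Conclusion.** The concern holds as an unresolved primary population, not as a demonstrated bias. The article gives two incompatible denominators for the rate tested against 13.5%. If enrollees are used, the chance of declaring success with no programme effect rises from 4.2% to about 30%, 67% or 98% at assumed consent odds ratios of 1.25, 1.5 or 2, taking 13.5% as the background rate in all eligible patients and 365 of 2300 consenting. If EMR patients are used, consent selection disappears, but the stated sample size, power and count of 54 no longer describe the test. Either way the primary success rule cannot be applied as written without a further decision. An analysis plan not shown here may make that decision, but the contradiction in the article would still need correcting.

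**What to change.** 1. State one primary population: all patients who meet the eligibility criteria that can be checked in the EMR, identified by the same EMR and visit rule in both phases, whether or not they consented.
2. Re-estimate the reference rate from the pre-intervention EMR phase under that same rule, or make the pre/post comparison under that rule the basis for the conclusion. Changing the population while keeping 13.5% is not enough, as step 4 of the working shows.
3. Replace the 54-of-317 rule and the power statement with figures for that population.
4. Report the 365 enrollees as a secondary population for the survey and factor analyses, with their uptake shown beside that of non-consenting patients in the same phase.
5. Bring Methods/design, Patient-level intervention approach, Data analyses of primary outcomes and Statistical power into line with this.

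The cost is protocol wording, a recalculation and an EMR query; the power section already says vaccination status can be read without consent. The downside is a diluted effect, because some EMR patients receive only the clinic-level components.

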## Discussion

The underutilization of HPV vaccination is a national problem that has been identified by the President’s Cancer Panel as a serious but correctable threat to the progress against cancer [31]. However, few studies have focused on the high-risk HIV population—an aging population that is increasingly managing other co-morbidities with their HIV diagnoses, including cancer. HPV vaccination is a form of primary cancer prevention that is imperative for a successful cancer control plan that may reduce the untimely death and clinical burden of HIV patients from several potentially vaccine-preventable HPV-related cancers including anal, cervical, vulvar, vaginal, penile, and oropharyngeal cancers. With an aging HIV population, it is an essential public health goal to provide the necessary resources and cancer prevention strategies for PLWH to achieve a normal life expectancy and quality of life. The CHAMPS study is the next step to achieving this goal for high-risk HIV-positive populations.

### Trial registration

NCT05065840; Registered on October 4, 2021.

## Data Availability

The datasets used and/or analyzed during the current study will be available from the corresponding author on reasonable request.

## Abbreviations

HPV: Human Papillomavirus
HIV/AIDS: Human Immunodeficiency virus/ Acquired immunodeficiency syndrome
PLWH: People living with HIV
MSM: Men who have sex with men
HAART: Highly active antiretroviral therapy
FDA: Food and Drug Administration
CDC: Centers for disease control and prevention
PP: Percentage points
CHAMPS: Advancing HPV vaccination in HIV positive adults
RE-AIM: Reach, Effectiveness/Efficacy, Adoption, Implementation, Maintenance
EMR: Electronic medical records
GRITS: Georgia Registry of Immunization Transactions and Services
CE: Continuing education
IC: Immunization champion
PASS: Power analysis & Sample size
